##### Child youth resilience measure-32

3.5.1.1.

The CYRM-32 is a 5-point Likert scale, optimized to assess resilience in children and young adults (aged 12–23). It has been previously shown that Cronbach’s *α* for the scale was 0.88, Confirmatory factor analysis supported a three-factor solution: family interaction (0.79 Cronbach’s *α*), interaction with others (0.72 Cronbach’s *α*) and individual skills (0.78 Cronbach’s *α*). Pearson correlation to assess temporal stability over 2 months was 0.695 (Llistosella et al., 2019).

##### Brief resilience scale

3.5.1.2.

The BRCS scale (Limonero et al., 2014; 4-items) is also a 5-point Likert scale to assess coping strategies to manage stress. Cronbach’s *α* for the scale was 0.7. Temporal stability at 6 weeks was measured by Pearson’s correlation, and its value was 0.69.

#### Secondary outcomes

3.5.2.

As secondary outcomes, we will evaluate the emotional regulation strategies through The Emotion Regulation Questionnaire (ERQ; Gross and John, 2003), and sadness symptoms through the assessment of a single item *“Are you depressed or sad?”* (Chochinov et al., 1997).

##### Emotion regulation questionnaire

3.5.2.1.

The ERQ will be used to assess two emotional regulation strategies: cognitive reappraisal (6 items) and expressive suppression (4 items). Participants will report using a 7-point Likert scale (1 = strongly disagree, 7 = strongly agree). Cronbach’s *α* coefficients were 0.75 (Suppression) and 0.79 (Reappraisal). Pearson coefficient was used to evaluate test–retest reliability over 3 months, and the values were 0.66 (Suppression) and 0.64 (Reappraisal; Gross and John, 2003).

##### Depressive symptoms

3.5.2.2.

Depressive mood will be asked as follow: *“Are you depressed or sad?.”* It was adapted from the “Are you depressed?” Screening for depression in the terminally ill (Chochinov et al., 1997). It evaluates through a numerical scale of 0–10 (0-not depressed, 10-worst possible depression).

##### Sociodemographic variables

3.5.2.3.

Adolescents will be asked to self-report sociodemographic variables: age, gender, ethnicity and family structure.

### Sample size calculation

3.6.

Standard deviation (SD) of the primary outcome CYRM-32 scale was used to estimate the minimum sample required to detect a 10-point difference in the scale between the intervention and control groups.

Taking into account an SD of 20 of the CYRM-32 scale, accepting an alpha risk of 5%, power of 80% and a follow-up loss rate of 10%, it would be necessary a minimum of 70 students/group. GRANMO tool (Antaviana, 2011) was used to calculate the sample size.

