**Methods:**

The recruitment period started in January 2022. Schools will be randomly allocated to control and intervention groups by an external researcher using computer-generated random numbers. The minimum sample size was estimated to be 70 participants per group. Primary health care nurses will carry out the intervention during the school period (January to June 2022). Students will follow a specific training consisting of six 55-min sessions, for 6 weeks. Each session will consist of 5 min of mindfulness, followed by 45 min of the corresponding activity: introducing resilience, self-esteem, emotional regulation strategies, social skills, problem-solving, community resources, social and peer support, and 5 min to explain the activity to do at home. Data will be collected at baseline, 6 weeks, and 24 weeks after the intervention. The child youth resilience measure-32 (CYRM-32) scale will be used to assess the effectiveness of the intervention. This study received a grant in June 2021.

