### Design

3.1.

This study is a cluster-randomized controlled trial with parallel arms. Clusters will be school classrooms (grades 6, 7), subjects aged 12-to-15 years.

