### Randomization

3.7.

Eligible schools will be randomly assigned to the intervention or control group. The clusters will be school classrooms (grades 6 and 7). For each grade (6 and 7) there will be several classrooms (clusters) depending on the schools. The randomization procedure will be performed in two steps. First, the schools will be randomly allocated either to an intervention group or control group by the external researcher using computer-generated random numbers; second, the external researcher will randomize the intervention group into the different school levels.

According to the minimum estimated sample size (70 participants/group) and knowing that there are 25 to 30 students per classroom, we will need a minimum of three clusters (classrooms) per group.

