In the application of this intervention, we consider some limitations. On one hand, the effect of the intervention may be lost in the long term. However, a 24 weeks follow-up is proposed to assess the maintenance of the effect and see if it is necessary to include reinforcement or repeat the intervention after 1 or 2 years to maintain resilient results. On the other hand, there may be some disparities in the effectiveness of the intervention between schools due to the different teams involved. If this is the case, we will propose to improve the trainings so that the teams act as similarly as possible.

Once the intervention will be applied, we will be able to assess its effectiveness. We expect to increase resilience in adolescents at risk and prevent mental health problems through this school-based intervention. Once the effectiveness is demonstrated, nurses from different fields such as primary health care or mental health specialists will have access to the program to be implemented in schools or other sites that work with adolescents at risk. This intervention will give new tools to nursing professionals to increase resilience and coping skills for facing adverse situations during adolescence.

Currently, we have finished the recruiting period and the trial status is “active” at www.clinicaltrials.gov. At the end of the recruitment, we had a total sample of 674 participants from eight randomized schools. The intervention was carried out in 4 schools from January 2022 to spring 2022. We are analyzing the initial data from control and intervention groups at T1 (baseline) and T2.

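### The 70 students per group is an individually randomised sample size with no design effect, so the stated minimum of three classrooms per group does not deliver 80% power in this cluster trial

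*Protocol article*

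**What the plan says.** Section 3.1 (Design) describes the trial thus: "This study is a cluster-randomized controlled trial with parallel arms. Clusters will be school classrooms (grades 6, 7"). Section 3.7 (Randomization) places the allocation one level higher: "First, the schools will be randomly allocated either to an intervention group or control group by the external researcher".

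Section 3.6 (Sample size calculation) sets out to "estimate the minimum sample required to detect a 10-point difference in the scale between the intervention and control groups". Its SD is given by "Taking into account an SD of 20 of the CYRM-32 scale", with an alpha of 5%. The result is "power of 80% and a follow-up loss rate of 10%, it would be necessary a minimum of 70 students/group". The Abstract repeats it: "The minimum sample size was estimated to be 70 participants per group".

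Section 3.7 then divides the 70 by a class size of 25 to 30 and concludes that "we will need a minimum of three clusters (classrooms) per group". Section 3.4.1 has the training take place in four schools. Section 4 (Discussion) reports that recruitment is over: "we had a total sample of 674 participants from eight randomized schools", with the intervention delivered in four of them.

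**The concern.** Students in the same school tend to resemble each other, so a trial that allocates schools needs more students than one that allocates individuals, and its precision is limited by the number of schools. Section 3.6 lists all its inputs, and none is an ICC, a cluster size or a number of clusters. In section 3.7 clusters appear only after the sample size is fixed, as a way of counting how many rooms hold 70 students.

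This is not a detail that an article leaves to a fuller document. The article gives a complete calculation with its result, and the result belongs to a different design. At stake is the power claim for the primary outcome, the Child youth resilience measure-32 (CYRM-32). A reader who sets 674 recruited against 140 required would take the trial to be heavily overpowered. That does not follow when only eight units were randomised.

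**Working it through.** **Inputs.** From section 3.6: difference 10, SD 20, alpha 5%, power 80%, loss 10%. From section 3.7: 25 to 30 students per classroom, at least three classrooms per group. From section 4: 674 students, eight schools, intervention in four. Assumed, because the article does not give them: the ICC (0.01 to 0.10) and, for the recruited trial, equal school sizes and four schools per arm.

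**1. The plan's own figure.** n = 2 × (1.96 + 0.8416)² × 20² / 10² = 62.8, rounded up to 63 per group; 63 / 0.9 = 70. This is an exact match. A one-sided test would give 50, then 56, and does not match. The independent-student formula thus accounts for the whole figure. Rounding up leaves slack for a design effect of only 63 / 62.8 = 1.003.

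**2. Formulas with clustering.** For k clusters per arm of m completers each:
- design effect DE = 1 + (m − 1) × ICC
- SE = √(2 × 400 × DE / (k × m))
- power for 10 points from 10/SE, by the normal distribution and by the noncentral t on 2(k − 1) df.

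**3. The stated minimum.** 63 completers per group in three classrooms: k = 3, m = 21, 4 df. Classrooms are treated as the clusters here, which is the lenient choice because schools are allocated.

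| ICC (assumed) | DE | Power, normal | Power, 4 df |
|---|---|---|---|
| 0 | 1.0 | 80% | 57% |
| 0.01 | 1.2 | 73% | 50% |
| 0.02 | 1.4 | 66% | 44% |
| 0.05 | 2.0 | 51% | 33% |
| 0.10 | 3.0 | 37% | 24% |

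The two columns separate two causes. The design effect alone takes 80% to 73% at ICC 0.01. The small number of clusters takes 80% to 57% before any correlation is assumed.

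**4. Three full classrooms.** With 30 enrolled in each, 27 complete (k × m = 81 per group). At ICC 0.01, DE = 1.26 and power is 81% (normal) or 57% (4 df). At ICC 0.02 it is 73% or 50%.

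**5. The trial as recruited.** 674 / 8 = 84.25 per school, and 84.25 × 0.9 = 75.8 completers; k = 4, 6 df. The difference detectable with 80% power is (2.447 + 0.906) × SE.

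| School ICC (assumed) | DE | SE | Power for 10 points, 6 df | Detectable difference |
|---|---|---|---|---|
| 0.01 | 1.75 | 2.15 | 97% | 7.2 |
| 0.02 | 2.50 | 2.57 | 90% | 8.6 |
| 0.03 | 3.25 | 2.93 | 81% | 9.8 |
| 0.05 | 4.74 | 3.54 | 66% | 11.9 |
| 0.10 | 8.48 | 4.73 | 43% | 15.9 |

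By normal approximation, power at ICC 0.05 is still 81%.

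**The case against.** The strongest reply is that the shortfall concerns a minimum that was never the trial. Recruitment closed at 674 students, nearly five times 140, and on 6 df that gives at least 80% power for 10 points up to an assumed ICC of about 0.03. This stands. A reader might infer from section 3.6 that the trial as run is underpowered; the article does not support that, because it gives no ICC.

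It is also fair to say that the 4-df figures should not be charged wholly to the missing design effect, since they start at 57% at ICC 0, and that three classrooms of 25 to 30 hold 75 to 90 students, more than 70. With three full classrooms and ICC 0.01, the normal approximation does reach 81%. The 4-df figure there is still 57%.

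A reader might also infer that three classrooms could all come from one school per arm. The minimum in section 3.7 would permit it, but section 3.4.1 plans the training in four schools, so the point should not rest on this. Nor does it follow that a null result would be uninterpretable: what such a result excludes comes from the confidence interval, which section 3.9 promises. Whether that interval allows for clustering is a question about the analysis.

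None of this restores the stated claim. The 80% attached to 70 per group still requires an ICC of essentially 0.

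**Conclusion.** The point holds for the stated minimum. The arithmetic in section 3.6 is right for independent students and wrong for a trial that allocates schools. With 70 per group in three classrooms, power is below 80% at any ICC above 0, apart from the trivial slack left by rounding: 73% down to 37% by normal approximation, and 50% down to 24% on 4 df, over ICC 0.01 to 0.10.

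For the recruited trial the conclusion is conditional. Power for 10 points runs from 97% to 43% and the detectable difference from 7.2 to 15.9 points over the same ICC range, so whether 80% is reached depends on a value the article does not state. These figures assume four schools per arm of equal size, 10% loss, SD 20 and no covariate adjustment. Unequal school sizes would lower power somewhat.

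**What to change.** Leave enrolment as it is and amend the text.

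- In section 3.6 and the Abstract, keep the 70 per group on record as the planning figure and say that it assumed independent students and made no allowance for clustering.
- Add the power for 10 points, or the detectable difference, for eight schools (four per arm), 674 students and 10% loss on 6 df. Give it over a stated ICC range with the source of that range, and label it as computed after recruitment.
- In section 3.7, remove three classrooms per group as a sufficient minimum, and name the school as the unit that limits precision.
- Do not credit the new figure with a baseline adjustment. Section 3.9 says only that regression with other variables will be considered, and it does not name the baseline score.

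The cost is a few sentences and one small table. The stated power will look less favourable at the higher ICCs.

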### Randomization

3.7.

Eligible schools will be randomly assigned to the intervention or control group. The clusters will be school classrooms (grades 6 and 7). For each grade (6 and 7) there will be several classrooms (clusters) depending on the schools. The randomization procedure will be performed in two steps. First, the schools will be randomly allocated either to an intervention group or control group by the external researcher using computer-generated random numbers; second, the external researcher will randomize the intervention group into the different school levels.

According to the minimum estimated sample size (70 participants/group) and knowing that there are 25 to 30 students per classroom, we will need a minimum of three clusters (classrooms) per group.

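### The school is the unit allocated to arm, but the protocol names the classroom as the cluster and sets its minimum size in classrooms; the grade step is described for one arm only

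*Protocol article*

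**What the plan says.** On the unit of allocation the protocol is consistent. The Abstract (Methods) states: "Schools will be randomly allocated to control and intervention groups by an external researcher using computer-generated random numbers". Section 3.7 repeats it. The Control group section (3.4.2) speaks of control schools, and the Discussion reports 674 participants from eight randomized schools, with the intervention delivered in four.

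On the cluster it says something else. Section 3.1: "Clusters will be school classrooms (grades 6, 7), subjects aged 12-to-15 years". Section 3.7 puts the two units in consecutive sentences: "Eligible schools will be randomly assigned to the intervention or control group. The clusters will be school classrooms (grades 6 and 7").

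Section 3.7 then turns the sample size into a number of clusters. From 70 students per group and "knowing that there are 25 to 30 students per classroom", it concludes that "we will need a minimum of three clusters (classrooms) per group". No minimum number of schools is given.

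The second randomization step in 3.7 reads: "the external researcher will randomize the intervention group into the different school levels". No counterpart for control schools is described.

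Data analysis (3.9) lists t, Mann–Whitney and chi-square tests, with regression as a possibility. It names neither school nor classroom, and grade does not appear.

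**The concern.** In a cluster trial the cluster that governs the standard error is the unit that was randomized. Here that is the school. Three classrooms of one school were not allocated separately; they went to the same arm together and share whatever makes that school's pupils alike. Calling the classroom the cluster does two kinds of harm.

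- **Design.** The minimum is counted in units that were not allocated. Three classrooms can all sit in one school, and with one school per arm the intervention effect cannot be separated from the difference between two schools.
- **Analysis.** Anyone who adds a cluster adjustment and takes the protocol's definition at its word will adjust at classroom level. That removes only part of the problem, and the result will look as if clustering had been handled.

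The one-sided wording of the second step raises a lesser question. If levels were drawn in intervention schools but not in control schools, the grade mix, and with it age, could differ between arms.

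**Working it through.** **1. The plan's own figures.** Inputs from section 3.6: difference 10, SD 20, alpha 5% (two-sided reproduces the result), power 80%, loss 10%.

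n per group = 2 × (1.96 + 0.842)² × 20² / 10² = 62.8, rounded up to 63; 63 / 0.9 = 70.

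Classrooms: 70/25 = 2.8 and 70/30 = 2.33, both rounded up to 3. Both stated figures reproduce, and both carry a design effect of 1.

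**2. What three classrooms amount to in schools.** From the Discussion, 674/8 = 84.25 students per school. At 25 to 30 per class that is 84.25/30 = 2.8 to 84.25/25 = 3.4 classes. An average school therefore supplies about three classrooms, the whole stated minimum for an arm.

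**3. Error of a classroom-level adjustment.** The documents give no ICC and no count of classrooms per school, so these are assumptions: per arm 4 schools × 3 classes × 28 students (672 in total, against 674 recruited); total variance 1; school ICC s; class ICC c. Let w = c + (1 − s − c)/28.

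- True variance of an arm mean: s/4 + w/12 = (3s + w)/12.
- Expected estimate from 12 class means treated as independent: (9s/11 + w)/12.
- Ratio R = (3s + w)/(9s/11 + w).
- Approximate type I error: P(|t| > 2.074/√R) with 22 df.

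For (0.05, 0): w = 0.95/28 = 0.0339; R = 0.1839/0.0748 = 2.46; 2.074/1.57 = 1.32; error about 20%.

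| (school, class) ICC | R | Approximation | Simulation |
|---|---|---|---|
| (0.01, 0.01) | 1.41 | 9.5% | 9.2–9.7% |
| (0.02, 0.02) | 1.62 | 11.7% | 11.9–12.0% |
| (0.03, 0.03) | 1.74 | 13.1% | 13.0–13.6% |
| (0.05, 0) | 2.46 | 20.0% | 20.7–21.1% |
| (0.01, 0.04) | 1.27 | 7.9% | about 8% |
| (0, 0.03) | 1.00 | 5.0% | about 5% |

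The simulation column gives the spread over repeated simulations of 4,000 to 40,000 trials each. In the same simulations a t-test on the eight school means (6 df) held 4.6% to 5.2%.

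**4. The minimum restated in schools.** With the school as cluster, the design effect is 1 + (84.25 − 1) × ICC, applied to 63 and then divided by 0.9. This gives 129, 187, 363 and 654 students per arm at ICC 0.01, 0.02, 0.05 and 0.10, that is 2, 3, 5 and 8 schools per arm. These use normal quantiles. With so few schools the t distribution asks for more, so they are lower bounds.

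**5. Power of the recruited design analysed by school.** With m = 84.25 × 0.9 = 75.8 and 4 schools per arm, SE = 20 × √(2 × [1 + (m − 1) × ICC]/(4m)), referred to a noncentral t with 6 df. Power for 10 points is about 97%, 90%, 66% and 43% at the same four ICCs.

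**The case against.** The best reply is that the 9% to 21% belongs to an analysis nobody has planned. A reader might infer that it is the error rate of the trial's written test. It is not: section 3.9 names no cluster term, so an analyst who follows it adjusts for nothing, and that is a separate question. The wrong label does harm only when an adjustment is added at the level it names. This stands and limits the claim. It does not remove it, because the protocol presents the trial as cluster-randomized and an adjustment at the named level is the natural next step.

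The range also depends on how the ICC is split. When the class effect dominates, the error falls to about 8%, and to 5% with no school effect at all. Three classes per school is likewise an assumption, since 3.7 says the number varies by school. Both points stand.

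On the second step, a reader might infer that grade is in fact confounded with arm. The sentence is ambiguous: it could mean drawing one level, or spreading delivery across levels. Sections 3.1 and 3.7 name both grades without distinction by arm. Imbalance is possible, not shown. A reader might go further and infer that levels not drawn in intervention schools serve as controls and are contaminated. Nothing supports that: section 3.4.2 describes whole control schools, and the Discussion describes four of eight schools receiving the intervention.

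**Conclusion.** The point holds in this form. The protocol allocates schools and names classrooms as clusters, and the two statements stand side by side in section 3.7. The minimum of three classrooms per group does not guarantee more than one randomized unit per arm. A classroom-level adjustment would leave type I error at about 9% to 21% over the first four ICC pairs tabulated, and near nominal only if the school effect is close to nil. Those figures rest on assumed ICCs and on three classes of 28 in each of eight schools.

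Recruiting 674 rather than 140 students does not settle the matter, because the number of randomized units remains eight. Whether power is adequate turns on the unknown school ICC.

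The grade issue is a matter of unclear reporting with a possible consequence: step two is described only for the intervention group, and the document does not show whether the arms differ.

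**What to change.** - In 3.1 and 3.7, state that the cluster is the school (eight, four per arm) with classroom nested within it.
- Express the minimum in schools per arm, with the ICC assumed.
- In 3.9, make school the top-level unit: a school random effect or a school-level summary, with about 6 degrees of freedom.
- Describe what step two did in each arm. If grades differ between arms, restrict the comparison to grades present in both. Include grade as a fixed effect.

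Recruitment is finished and the intervention delivered, so the levels cannot be redrawn. What remains is wording and analysis. Grade is not among the listed sociodemographic variables (3.5.2.3) but should be identifiable from the classroom.

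The price is wider intervals. Relative to a 22-df classroom analysis the critical value alone rises from 2.07 to 2.45, a factor of 1.18, and the standard error grows as well where schools differ.

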### Blinding

3.8.

Given the difficulty in masking any condition, participant groups and personnel (research team) will not be blinded.

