Data collection will start in January 2022 and will finish in December 2022. Data will be collected at baseline, after 6 weeks of the intervention (Post-intervention I) and 24 weeks later (Post-intervention II; Figure 1). Data from participants will be obtained through self-reported questionnaires provided by researchers. Teachers at schools will assure the full completion of the questionnaires at the desired times (T1-T3). Data will be stored on a secure server during the study, following the Spanish regulations. Recruitment of participants will be reported according to CONSORT guidelines for clustered randomized trials (Ivers et al., 2011; Figure 2).

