### Data analysis

3.9.

An intention-to-treat analysis will be performed. A descriptive analysis of the variables will be carried out, with frequency and percentage for the qualitative variables; mean and standard deviation for the quantitative normal distributed variables and median and quartiles for the quantitative not-normal distributed variables. The values from the scores for the intervention and the control group will be compared with the *t*-student test if the score is normally distributed, with the Mann–Whitney test if the score is not-normally distributed and if the score has a cut-off, it will be compared with chi-square test. The effect size will be calculated as the difference of means and with ratio of proportions (with its corresponding confidence intervals).

A linear regression and a logistic regression will be considered including other variables that can affect the response. Also, we will stratify the results for other factors like gender, age and others than will be considered. To check normality, the Kolmogorov–Smirnov test and the Shapiro–Wilk test will be used. All the confidence intervals will be performed with a 95% confidence level. All the analysis will be performed with the software R version 4.2.2.

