### Consent process

5.2.

The study will be carried out in compliance with current legislation, by following the Biomedical Research Law 14/2007. The confidentiality of participants’ data will be guaranteed, in compliance with Organic Law 3/2018, of 5 December, on the Protection of Personal Data and the guarantee of digital rights and the General Data Protection Regulation (EU) 679/2016.

First, secondary school directors who will participate in this research will sign an agreement and attachment to the study. Second, an online session with parents/carers of the selected schools will be held to explain the study and the intervention. Third, before being registered for the study, the schools will send a letter with all relevant information about the study and the written informed consent form (in both languages, Catalan and Spanish, to parents/carers). Parents/carers will return the informed consent form (ICF) signed and they will keep a copy. ICF from participants will be obtained after an informative session (with age-appropriate information) in the classroom conducted by their teachers and the research team. If the parents/carers give consent, but the adolescents do not want to participate in the study, the decision of the participants will prevail and will be respected. For adolescents with difficulty with written information, visual information sheets will be provided. Each participant will be identified by a serial number and the initials of the first and last name. Only the principal investigator and collaborating researchers will have access to the collected data.

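### Section 3.8 leaves the whole research team unblinded for a reason that does not extend to data cleaning and analysis, where coded arm labels would suffice

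*Protocol article*

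**What the plan says.** Section 3.8 (Blinding) is a single sentence. It cites the difficulty of masking the condition and concludes that "participant groups and personnel (research team) will not be blinded". It makes no exception for data management or analysis.

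Other sections bear on who works with the data and what is left to decide:

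- Section 5.2 (Consent process): "Only the principal investigator and collaborating researchers will have access to the collected data".
- Section 4 (Discussion), on trial status: "We are analyzing the initial data from control and intervention groups at T1 (baseline) and T2". It also reports 674 participants from eight randomised schools, four of which received the intervention.
- Section 3.9 (Data analysis): "A linear regression and a logistic regression will be considered including other variables that can affect the response". No covariate is named, and the list of stratification factors is open-ended beyond gender and age. The choice between the t-test and its alternatives follows a stated condition: "with the Mann–Whitney test if the score is not-normally distributed and if the score has a cut-off, it will be compared with chi-square test".
- Section 3.7 (Randomization): schools are allocated "by the external researcher using computer-generated random numbers". Randomisation is the only step explicitly given to an external person.
- Section 3.3 (Study setting and data collection): "Data from participants will be obtained through self-reported questionnaires provided by researchers".

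**The concern.** The reason given in section 3.8 is narrower than the decision it supports. Pupils who attend the sessions, teachers who sit in on them and nurses who deliver them cannot be kept from knowing the condition. Someone who cleans a file or fits a model can be, because that work needs only a label such as A or B.

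The gap matters for two reasons. First, every outcome is self-reported by pupils who know their condition, and nothing can now mask that. Masking of cleaning and analysis is the blinding step still open to this trial. Second, the people with data access include the principal researcher, who trains the nurses and supervises them weekly (section 3.4.1), and the result decides whether control schools are offered the programme (section 3.4.2). If record-level cleaning, the decision to use regression, the covariates or the strata are settled by people who can see which arm gains, those decisions can drift towards one arm without anyone intending it.

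**Working it through.** The point rests on setting the sections side by side. The arithmetic shows only what can and cannot be quantified.

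**1. Whom the reason covers.** Difficulty of masking the condition applies to pupils, teachers, nurses and field staff. It does not apply to cleaning or analysis. Scoring fixed Likert items and a 0–10 item is mechanical, so masking adds little there. The exposure lies in cleaning, model, covariate and stratum decisions.

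**2. Who holds the data.** Section 3.8 unblinds the research team, section 5.2 restricts data access to the principal investigator and collaborating researchers, and section 4 says in the first person that T1 and T2 data from both groups are being analysed. Together these place the analysis with the unblinded team. This is an inference: section 3.8 does not name the analyst.

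**3. Which choices are open (section 3.9).**

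- Open: whether regression is used, with which covariates, and which strata beyond gender and age.
- Not open in the same way: t-test or Mann–Whitney, which follows from normality; chi-square, which applies to a score that has a cut-off; and the analysis population, stated as intention-to-treat.

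**4. Can an error rate be attached to the lack of masking?** Null trials were simulated with normal scores, independent pupils and a baseline–outcome correlation of 0.695 (the CYRM-32 two-month stability in section 3.5.1.1). A trial counted as significant if the smallest two-sided p-value among the analyses was below 0.05.

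- 337 per arm (674 / 2), 4,000 trials: fixed t-test 5.0%; test chosen mechanically by a Shapiro–Wilk rule 5.1%; best of t and Mann–Whitney 5.9%; adding one adjusted regression 8.6%; adding a median-split chi-square 10.4%.
- 303 per arm (674 × 0.9 / 2 = 303.3), 4,000 trials: fixed t-test 4.8%; best of t, Mann–Whitney and three regressions 9.9%; adding a median-split chi-square 12.3%; using chi-square at three cut-offs instead 16.2%.
- 303 per arm, 1,500 trials, recomputing every p-value with the arm labels swapped: the largest change in any p-value was 6e-14. The best-of rates were 9.3% (five analyses) and 11.6% (six).

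Two-sided p-values do not depend on which arm is called A. An analyst with a coded file who picked the smallest p-value would have the same error rate as one with an open file. These rates measure the cost of not fixing the analysis in advance. Masking withholds which arm a choice favours, and the documents offer no basis for putting a number on that.

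**5. Effect on sample size.** The plan's own figure reproduces: n = 2(1.96 + 0.842)² × 20² / 10² = 62.8, so 63 per group, and 63 / 0.9 = 70. Coding the arms does not change it.

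**The case against.** The strongest reply is that this is a pre-specification complaint filed under blinding. Covariates, strata and locking procedures commonly sit in a statistical analysis plan. Section 4 says a statistical expert developed one, and it is not shown. That reply stands as far as the open choices in section 3.9 go: their absence from a condensed article is not itself the finding. It does not dispose of section 3.8, which states a decision covering the whole team and gives a reason that does not reach the analysis. Nor does the monitoring committee in section 3.4.3 answer it. The committee checks accuracy and completeness, but nothing says that it codes or withholds the arms.

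Three stronger readings are tempting, and the documents do not support them.

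- A reader might infer that unmasked analysis raises the false-positive rate to 10–16%. It does not follow: those rates are unchanged when the labels are swapped. The upper end also assumes free choice among three cut-offs, which section 3.9 does not offer.
- A reader might infer that every analysis choice is made with the arm result in view. Section 3.9 ties the main test to normality, and that rule applied mechanically stays near 5%. It does not say when covariates and strata are fixed, and it offers no choice of exclusions.
- A reader might infer that T2 has already been compared between arms unmasked. Section 4 says only that data from both groups are being analysed. It does not say that effects were compared or that labels were uncoded.

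It is also fair that coded labels leave the larger threat, unblinded self-report, untouched.

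**Conclusion.** The point holds as a cheap improvement. Section 3.8 unblinds everyone for a reason that covers only those who receive, deliver or observe the intervention. Sections 3.9, 4 and 5.2 together mean that open analysis choices can be made by people who can see the arms. The conclusion assumes that the research team in section 3.8 includes those who clean and analyse the data, which sections 4 and 5.2 imply but do not state. It also assumes that no unshown plan provides for coded data.

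The text shows exposure to bias, not that any choice was biased. No numerical size is claimed, and the results are not invalidated on this ground.

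**What to change.** Amend section 3.8 along these lines:

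- Pupils, teachers, nurses and field staff are not blinded. Cleaning and analysis use a file with arms coded A and B and schools replaced by codes; because allocation is by school, a school name reveals the arm.
- The external researcher who did the allocation holds the key until the primary model, covariates, strata and missing-data handling are fixed and dated. Fixing these choices is what controls selection among analyses. The code keeps direction out of sight while they are made.
- No T3 comparison between arms is made before those choices are locked.
- For T1 and T2, the article states who has seen results by arm and when the analysis choices were fixed. Any choice made after arm-level results were seen is labelled post hoc.

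The cost is a paragraph of text and a recoded dataset. No new staff are needed, and the sample size is unchanged. The limits should be stated too: full protection may apply only to T3, a two-arm code may be guessed, and bias from unblinded self-report remains.
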